### Interim analyses {21b}

No interim analyses are scheduled for this trial. However, an independent data monitoring committee (DMC) periodically will receive an overview of the current safety data. Individual patients may be withdrawn from the trial if one or more of the following criteria are met:
Withdrawal of consent on the part of the patient or legal representativeAdverse events (including intercurrent illnesses) which preclude further treatment with the IMP or make further participation in the clinical trial inadvisablePremature termination considered to be medically indicatedPregnancySignificant violations of the trial protocol or lack of compliance on the part of the patient

A treatment arm or the entire clinical trial may be terminated prematurely if:
Following a safety analysis by the DMC, the sponsor or the coordinating investigator consider that the risk-benefit ratio for trial patients has changed significantlyQuestion(s) addressed in the trial can be clearly answered on the basis of the results of another trial on the same subjectsThe recruitment rate is insufficient, defined as < 3 patients recruited within the first 9 months

### Methods for additional analyses (e.g., subgroup analyses) {20b}

Not applicable, no subgroup or adjusted analysis is planned.

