### Trial design {8}

This is a mono-center, randomized, controlled, parallel-group, open-label phase II trial. Fifty-four patients will be randomized at a ratio of 1:1 to receive either standard of care or standard of care plus the IT (Fig. 1).

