**Fig. 2 Fig2:**
[figure not shown]
Therapy protocol in group 2

**Table 3 Tab3:** Dosing regimen of investigational medicinal products

Study medication	Pharmaceutical form and route of administration	Duration/regimen
Urokinase diluted in Ringer’s solution	Intrathecal use	Continuous cisternal lavage with 100 I.U. urokinase per ml Ringer’s solution at a rate of ~ 50 ml/h for 7 days following implantation of the catheter, i.e., from day 2 ± 2 until day 9 ± 2 after aSAH, or until the onset of cerebral vasospasm or DIND. Total daily dose: 120.000 I.U. Note: urokinase administration has to be stopped when nimodipine is given.
Nimodipine diluted in Ringer’s solution	Intrathecal use	Nimodipine is given on demand in case of vasospasm (i.e., delayed ischemic neurological deficit or mean flow velocities of any intracranial vessel > 120 cm/s on Doppler ultrasonography). In this case, nimodipine is administered as continuous cisternal lavage with 0.005 mg nimodipine per ml Ringer’s solution at a rate of ~ 50 ml/h. Nimodipine infusion is performed from the onset of vasospasm to the cessation of vasospasm, at least, however, for 24 h. If necessary, nimodipine can be administered as often as necessary or for extended periods during aSAH treatment (up to the entire aSAH treatment phase of this trial, i.e., up to 21 days). Total daily dose: 6 mg. Note: urokinase administration has to be stopped when nimodipine is given.
Ringer’s solution	Intrathecal use	Continuous cisternal lavage with Ringer’s solution at a rate of ~ 50 ml/h, starting from day 9 ± 2 (i.e., from the end of urokinase therapy) to day 18 ± 3 after aSAH; the exact stop date will be determined based on the investigator’s risk-benefit assessment for the individual patient. The criteria for this assessment are risk of catheter infection, macroscopic clearance of lavage fluid (i.e., no or minimal residual xanthochromia), and individual risk assessment for the development of vasospasm beyond day 15, considering patient neurological status, WFNS grade, sex, age, blood amount, and course of transcranial Doppler ultrasonographic measurements.

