### Sample size {14}

The sample size calculation is based on the primary endpoint dichotomized mRS (mRS > 3) with an expected proportion of 50% in the standard-of-care group and 15% in the experimental treatment group. These assumptions are based on the first results of individual off-label treatments with the new procedure as described by [name] et al. [17, 19].

The study is planned to detect a difference between the experimental and control groups with respect to dichotomized mRS (mRS > 3) with a power of 80% using the two-sided *χ*^2^ test at a two-sided significance level of 5%. The null hypothesis is rejected if the asymptotic two-sided 95% confidence interval for the odds ratio (control vs. experimental) does not contain one. Under these assumptions, 54 patients are required for analysis.

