## Assignment of interventions: allocation

### Sequence generation {16a}

Randomization will be performed at a ratio of 1:1. The randomization code will be generated using the electronic, web-based tool randomizer.at (https://randomizer.at/). Block randomization will be performed. The block length will be documented separately and will not be disclosed to the site.

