## Discussion

DCI is a major cause of death and poor neurological outcome in patients with aSAH. The therapeutic armamentarium currently available to address this problem is narrow and insufficient. Thus, there is a significant need to develop new treatment approaches for these patients.

Direct intrathecal therapies with fibrinolytic (e.g., urokinase) and spasmolytic agents (e.g., nimodipine) have appeared promising in clinical trials. However, in patients with aneurysms secured by endovascular intervention (coiling) which is the dominant technique of aneurysm securing today, no safe method of access to the very target of this therapy exists.

We introduce STX-VCS to establish a cisternal treatment access irrespective of the method of aneurysm securing and propose a stepwise protocol for cisternal drug delivery. The pathophysiologic rationale of our approach is to remove the presumed trigger for CVS through fibrinolysis of subarachnoid blood clots and to target CVS directly in case it occurs. Furthermore, as ventricular blood presents an add-on risk for vasospasm [21], it appears plausible to involve the ventricles in the lavage circuit and hence to establish a ventriculo-cisternal lavage. We propose this RCT to assess the clinical safety and efficacy of this approach.

Additionally, the majority of DCI cases occur in patients of WFNS grade 5 (68% of DCI cases in our institutional series). By including WFNS 5 patients, the present trial is designed to be offered to (nearly) all patients at risk for DCI, i.e., WFNS 3–5. This approach differs from most other recent and ongoing RCTs on CVS and DCI which typically exclude WFNS 5 patients.

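### Adjusted analysis is ruled out in a 54-patient trial with no strata described; pre-specifying WFNS grade and age as covariates would be a cheap, modest improvement

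*Protocol article*

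**What the plan says.** Section {20b} of the protocol article states: "Not applicable, no subgroup or adjusted analysis is planned". Section {20a} fixes the primary analysis as a logistic regression with an asymptotic 95% confidence interval for the odds ratio and names no covariate. It leaves details to an analysis plan finalized after recruitment.

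Section {16a} says "Block randomization will be performed" and names no stratification factor. Section {8} says "Fifty-four patients will be randomized at a ratio of 1:1".

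The inclusion criteria (Table 2) cover WFNS grades 3 to 5 and ages from 18 to under 80, so both are recorded before randomization. In two places the article treats such variables as markers of risk. Table 3 has the investigator judge the risk of late vasospasm "considering patient neurological status, WFNS grade, sex, age, blood amount". The Discussion attributes 68% of DCI cases in the institution's own series to WFNS grade 5.

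**The concern.** With 27 patients per arm and no strata described, balance on admission severity is left to chance. Section {20b} then also excludes the analysis that could use severity. If the arms differ in their share of WFNS 5, the protocol offers no pre-specified estimate that allows for it. An adjustment added later, in an open-label trial, would carry little credibility.

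Two things are at stake. One is a small amount of power, in a design with none to spare. The other is a pre-specified answer to the question of whether the arms were comparable.

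**Working it through.** **1. Planned sample size.** The inputs in section {14} are two-sided 5%, 80% power, and a primary endpoint (mRS > 3) "with an expected proportion of 50% in the standard-of-care group and 15% in the experimental treatment group". With pooled variance and no continuity correction, the mean risk is (0.50 + 0.15)/2 = 0.325 and

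n per arm = [1.960·√(2·0.325·0.675) + 0.842·√(0.50·0.50 + 0.15·0.85)]² / 0.35² = 26.9, rounded up to 27.

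That gives 54, so "Under these assumptions, 54 patients are required for analysis" reproduces. Exact power with 27 per arm is 82.0% for the chi-square test, but 78.3% for the asymptotic (Wald) interval for the odds ratio that decides the test.

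**2. Chance imbalance.** Assume that half the patients are WFNS 5; the article gives no mix.
- If each patient is independently WFNS 5 with probability 0.5, a gap of 6 or more patients (6/27 = 22 points) has probability 13.4%.
- If exactly 27 of the 54 are WFNS 5, the probability is 10.2%.
- If exactly 22 or 32 are WFNS 5 (shares of about 40% or 60%), it is 16.6%.

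**3. What a gap would do.** Assume an overall risk of 50% with half the patients WFNS 5. For a WFNS 5 odds ratio of R against grades 3 and 4, the two risks are √R/(1+√R) and 1/(1+√R). A 20-point gap shifts the risk difference by 0.20 times their difference:
- R = 4: 0.20 × (0.667 − 0.333) = 6.7 points
- R = 9: 0.20 × (0.75 − 0.25) = 10 points
- R = 16: 0.20 × (0.80 − 0.20) = 12 points

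The planned effect is 35 points.

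**4. Power with and without adjustment.** The simulations use 27 per arm, with marginal risks held at 50% and 15%. Adjusted models contain WFNS 5 versus 3–4 and age. The covariate effects are assumptions; age odds ratios are per standard deviation.

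| Assumed covariate effects | Unadjusted, Wald | Adjusted, ordinary Wald | Adjusted, Firth with Wald | Adjusted, Firth with profile likelihood |
|---|---|---|---|---|
| None | 79% | 78% | 75% | 79% |
| WFNS 5 OR 3 | 77% | 79% | 76% | 80% |
| WFNS 5 OR 5, age OR 1.65 | 78% | 83% | 80% (separate run) | 84% |
| WFNS 5 OR 9, age OR 2 | 78% | 85% | – | – |

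A run of 2,000 trials has a standard error of √(0.8·0.2/2000) = 0.9 points, so differences of 1 point mean nothing.

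The second and third columns give the like-for-like effect of the covariates: about 0 to 5 points for WFNS 5 odds ratios of 1 to 5. The last column also changes the interval, and step 1 shows that the Wald interval alone costs 82.0 − 78.3 = 3.7 points against chi-square. Its whole gain should therefore not be credited to adjustment.

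A separate simulation, with WFNS as a three-level score and no age term, agrees. The gain was about 0 points at an odds ratio of 1 per grade, 0.6 to 0.9 at 1.5, 1.5 to 2.7 at 2, and 3.8 to 5.1 at 3.

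**5. Type I error.** In the three-level simulation, the unadjusted Wald test rejected in 3.5 to 4.5% of null trials and the ordinary adjusted test in 3.8 to 5.2%. With both covariates, the ordinary adjusted test rejected in about 4.5 to 5.5%. A check of the Firth profile-likelihood test under the null gave no sign of inflation.

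**6. Room for covariates.** Expected unfavourable outcomes: 27 × 0.50 + 27 × 0.15 = 17.6.

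**The case against.** The strongest reply is that nothing here is wrong. An unadjusted logistic model matches an unadjusted sample size calculation, is valid under randomization, and is stated in advance. Excluding adjusted analyses also blocks the choice of covariates after the event, in an open-label trial whose analysis plan is finalized late. This stands, and it is why the point is an improvement.

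A reader might infer that imbalance in WFNS 5 could create or hide the treatment effect. The documents do not support that. In null simulations restricted to gaps of 6 or more WFNS 5 patients, the unadjusted test rejected in about 5.5% of trials at an odds ratio of 3. At an odds ratio of 5 with an age effect it rejected in about 9% (only 260 such trials, so imprecise). Power in such trials was 80% and 70% respectively. The distortion is real but moderate, and arises in a minority of trials.

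A reader might also infer that the article establishes WFNS grade and age as strong predictors of the primary endpoint. It does not. Table 3 concerns vasospasm beyond day 15. The 68% is a share of DCI cases with no denominator; at an assumed 50% prevalence it implies a risk ratio of 68/32 = 2.1, for DCI and not for 6-month mRS. The larger gains in the table rest on assumed odds ratios.

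Nor is the gain free. Firth estimation with Wald intervals loses power when the covariates are weak. Ordinary adjusted fits separated in 1.5 to 3.5% of simulated trials under the planned effect.

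Finally, the absence of strata is read from silence in section {16a}. Section {49}-style deferral to another document is not offered for this item: section {31c} presents the publication as the public access to the full protocol, which supports the reading without proving it.

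**Conclusion.** The point holds as a recommendation. Section {20b} closes off a pre-specified adjustment that would use data already recorded. The benefit is about 0 to 5 points of power at assumed WFNS 5 odds ratios of 1 to 5, and more only if the covariates are very strong. It also supplies a correction for chance imbalance fixed in advance.

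The planned unadjusted test remains valid, and leaving covariates out does not inflate its type I error. The sizes rest on an assumed WFNS mix and on assumed covariate effects on mRS, neither of which the article gives.

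**What to change.** Replace the sentence in {20b} and amend {20a} so that:
- the primary logistic model contains treatment, WFNS grade (5 versus 3–4) and age (continuous);
- it is fitted by Firth penalised likelihood, with a profile-likelihood (not Wald) 95% confidence interval and test;
- the covariates are fixed before anyone sees outcomes by arm;
- the unadjusted odds ratio is kept as a sensitivity analysis;
- standardized risks per arm and their difference are reported.

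The rejection rule in {14}, which refers to the asymptotic interval, should be aligned. Since {20a} handles missing primary outcomes by multiple imputation, the analysis plan should also say how profile-likelihood results are combined across imputations.

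The cost is wording in the protocol and analysis plan; no new data are needed. The odds ratio becomes conditional on the covariates, which is why the standardized risks belong beside it. With 17 to 18 expected unfavourable outcomes, these two covariates are the limit.

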### Methods in analysis to handle protocol non-adherence and any statistical methods to handle missing data {20c}

Efficacy analyses will be performed primarily in the full analysis set (FAS) according to the intention-to-treat (ITT) principle. This means that the patients will be analyzed in the treatment arms to which they were randomized, irrespective of whether they refused or discontinued the treatment or whether other protocol violations occurred.

The analysis of the per-protocol (PP) population will be performed for the purpose of a sensitivity analysis. The PP population is a subset of the FAS and is defined as the group of patients who had no major protocol violations, received a predefined minimum dose of the treatment, and underwent the examinations required for the assessment of the endpoints at relevant, predefined times.

Safety analyses will be performed in the safety population. Patients in the safety population are analyzed as belonging to the treatment arm defined by treatment received. Patients are included in the respective treatment arm, if treatment was started.

### Plans to give access to the full protocol, participant level-data, and statistical code {31c}

Public access to the full protocol is granted by way of the present publication. Participant-level data may be made available upon reasonable request, and as far as permitted by data protection legislation.

## Oversight and monitoring

### Composition of the coordinating center and trial steering committee {5d}

The principal investigator and his deputy are responsible for the following:
Design and conduct of the study and general study oversightPreparation of protocol and revisionsPreparation of investigators brochure (IB)Publication of study reports

The Clinical Trials Unit of the Medical Center, University of Freiburg, under the supervision of the principal investigator, is responsible for the following:
Project management, i.e., regulatory compliance, preparation of submissions to competent authorities, finance and contract management, maintenance of trial master file, coordination of study team meetingsData management, i.e., design, validation, and maintenance of case report forms and study databasePharmacovigilance, i.e., adverse event reporting to the national competent authorityClinical monitoring, source data verification, and quality managementPlanning and performance of statistical analyses

### Composition of the data monitoring committee, its role, and reporting structure {21a}

Additionally, an independent Data Monitoring Committee (DMC) has been established to monitor the course of the trial, to evaluate the risk threshold and the degree of distress for trial patients, and to give recommendations to the sponsor regarding discontinuation, modification, or continuation of the trial. Data evaluated by the DMC are specified in detail in a DMC charter which can be found in Additional File 2.

### Adverse event reporting and harms {22}

An adverse event (AE) is any untoward medical occurrence in a patient administered any dose of a pharmaceutical product which does not necessarily have a causal relationship with the use of the product. An AE can therefore be any unfavorable and unintended sign (including an abnormal laboratory finding), symptom, or disease temporally associated with the use of an IMP, whether or not related to the product.

In order to monitor the conditions of the patients from the time the patients receive the catheter implantation, the investigator is requested to report any untoward clinical event on the AE page of the CRF. Irrespective of any causal relationship, all AEs spontaneously reported by the patient or observed by the investigator will be documented in the case report form starting from randomization until the end of the study (month 6).

All AEs must be described by diagnosis or, if an underlying diagnosis is not known, by symptoms or medically significant laboratory or instrumental abnormalities. Symptoms, medically significant laboratory, or instrumental (e.g., electrocardiographic) abnormalities of a pre-existing disease are not considered an AE. Occurrences of new symptoms or laboratory or instrumental abnormalities, as well as worsening of pre-existing ones, are considered AEs. All AEs, no matter how intense, are to be followed up by the investigator in accordance with ICH-GCP until resolved or judged no longer clinically relevant or, in case of a chronic condition, until it is fully characterized.

For any AE, the following will be documented:
Characterization of the event (diagnosis; if not available, symptoms)Onset/end dateSeverity according to the common classification: (1) mild, (2) moderate, (3) severe, (4) life-threatening/disabling, and (5) deathRelationship to the IMP(s) (related/not related) or to study-specific procedures (such as stereotactic surgery or intrathecal lavage)Serious/non-seriousAction taken with IMP(s)Outcome

In this clinical trial, the following adverse events will be pre-specified (e.g., as a drop-down menu) for documentation in the CRF:
Delayed ischemic neurological deficit (DIND)DCIHydrocephalus requiring shunt implantationEndovascular interventions for the treatment of cerebral vasospasmComplications after aneurysm securingIntracerebral hemorrhageRe-SAHIntracerebral infection (meningitis and/or encephalitis)Episodes of critically increased ICP

During each visit, it will be actively evaluated whether one of these events occurred since the last study visit.

Serious adverse events (SAEs) are subject to additional documentation and expedited reporting requirements as given by German legislation. An SAE is defined as any untoward medical occurrence that results in one or more of the following outcomes:
DeathLife-threatening situation (patient is at immediate risk of death), inpatient hospitalization, or prolongation of existing hospitalization (excluding those for study therapy and/or assessments, placement of an indwelling catheter, social/convenience admissions, respite care, elective or pre-planned treatment/surgery)Persistent or significant disability/incapacityCongenital anomaly/birth defectOther medically important conditions: conditions which, in the investigator’s opinion, may not be immediately life-threatening or result in hospitalization but may jeopardize the patient’s safety or may require intervention to prevent one of the other outcomes listed in the definition above, may also be considered serious. Examples of such conditions include allergic bronchospasm requiring treatment in an emergency room or at home, unexpected convulsions (i.e. convulsions which cannot be explained by the underlying illness) that do not result in hospitalization, development of IMP dependency or drug abuse, and suspected transmission of infectious agents by a medicinal product

In sum, established guidelines and definitions, standard operating procedures, and applicable laws and regulations will be followed in the documentation and reporting of adverse events. The results of the safety analyses described above will be reported in trial publications.

### Frequency and plans for auditing trial conduct {23}

Audits may be performed according to local quality assurance requirements in order to determine whether appropriate processes are in place and are laid down in standard operating procedures (system audit); whether such processes are carried out in a way that is reasonable, comprehensive, and in line with applicable regulation; whether the responsible personnel is appropriately qualified to take on their tasks (process audit); and whether important documents (e.g., clinical trial protocol, case report forms) comply with all relevant local and regulatory provisions (product audit). Such evaluations may take the form of internal (e.g., the Clinical Trials Unit being audited by its own quality assurance department) or external audits (e.g., the Clinical Trials Unit auditing the Department of Neurosurgery, or the central department for governance and quality of the Medical Center, University of Freiburg, auditing the Clinical Trials Unit or the Department of Neurosurgery).

### Plans for communicating important protocol amendments to relevant parties (e.g., trial participants, ethical committees) {25}

Substantial amendments to the trial protocol (e.g., changes to eligibility criteria, outcomes, analyses) will only be implemented after CA and EC approval has been obtained. Changes to the protocol that are required for patient safety may be implemented prior to CA and EC approval. In case of protocol amendments, the relevant entry in the trial registry will be updated accordingly.

### Dissemination plans {31a}

Upon trial completion, the results of this trial will be submitted for publication in a scientific journal, presented at academic conferences, and posted in a publicly accessible database of clinical trial results irrespective of the results of the trial. No contractual restrictions exist regarding the publication of trial results. In line with ICMJE recommendations on authorship, the authors of the main publication shall be all those who have made significant intellectual contributions to the design and conduct of the study, or to acquiring, interpreting, and analyzing the study data. It is not intended to engage professional writers for publications of this trial.

